## Abstract

**Background:**

In patients with epilepsy, poor adherence to anti-epileptic drugs has been shown to be the most important cause of poorly controlled epilepsy. Furthermore, it has been noted that the quality of life among patients with epilepsy can be improved by counseling and treatments aimed at increasing their self-efficacy and concordance, thus stimulating self-management skills. However, there is a need for evidence on the effectiveness of such programs, especially within epilepsy care. Therefore, we have developed a multi-component intervention (MCI) which combines a self-management/education program with e-Health interventions. Accordingly, the overall objective of this study is to assess the (cost)-effectiveness and feasibility of the MCI, aiming to improve self-efficacy and concordance in patients with epilepsy.

**Methods:**

A RCT in two parallel groups will be conducted to compare the MCI with a control condition in epilepsy patients. One hundred eligible epilepsy patients will be recruited and allocated to either the intervention or control group. The intervention group will receive the MCI consisting of a self-management/education program of six meetings, including e-Health interventions, and will be followed for 12 months. The control group will receive care as usual and will be followed for 6 months, after which patients will be offered the possibility of participating in the MCI. The study will consist of three parts: 1) a clinical effectiveness study, 2) a cost-effectiveness study, and 3) process evaluation. The primary outcome will be self-efficacy. Secondary outcomes include adherence, side effects, change in seizure severity & frequency, improved quality of life, proactive coping, and societal costs. Outcome assessments will be done using questionnaires at baseline and after 3, 6, 9, and 12 months (last two applicable only for intervention group).

**Discussion:**

In times of budget constraints, MCI could be a valuable addition to the current healthcare provision for epilepsy, as it is expected that higher concordance and self-efficacy will result in reduced use of healthcare resources and an increased QOL. Accordingly, this study is aimed helping patients to be their own provider of health care, shifting epilepsy management from professionals to self-care by patients equipped with appropriate skills and tools.

**Trial registration number:**

NTR4484.

## Background

Epilepsy is a chronic disorder of the brain, characterized by recurrent seizures. Seizures are the result of sudden, excessive electrical discharges in a group of brain cells. Different parts of the brain can be the site of such discharges, resulting in a variety of clinical manifestations [1].

Epilepsy has a considerable psychological and emotional impact, which is strongly reflected in a reduced quality of life (QOL) for patients suffering from epilepsy [2,3]. Living with seizures is likely to affect patients’ daily activities, as it interferes with many aspects of everyday life. Furthermore, epilepsy has been shown to have a large economic impact on society as a whole [4,5]. For example, the unemployment rate among epileptic patients is at least twice as high as in the general population [6-8].

Recent studies have shown that up to 70-80% of newly diagnosed epilepsy patients can be treated successfully (i.e. seizures completely controlled) with anti-epileptic drugs (AEDs) [9-11] and it is estimated that currently more than 80,000 patients in the Netherlands are treated with AEDs [12]. However, to achieve and maintain successful seizure control, adherence to treatment is of major importance. A systematic review argued that effective ways of helping people follow medical treatments could have far larger effects on health than any treatment itself [13]. In addition, it has been recommended that the cost-effectiveness of adherence interventions should be a research priority in the field of chronic diseases [14]. In epilepsy, poor adherence has been shown to be the most important cause of poorly controlled epilepsy [15]. However, this study is striving to improve ‘concordance’ and not only ‘adherence’. The crucial difference is that ‘adherence’ describes only the extent to which a patient takes antiepileptic drugs as prescribed with respect to dosage and dosing intervals [16], while ‘concordance’ includes a consensual agreement about taking AEDs that has been established between patient and practitioner [17].

Concordance with medical treatment is closely linked with the patients’ ability to self-manage their disease, and the latter is shown to be an important factor in determining quality of life [18]. Self-management programs focus on supporting patients in coping with their chronic condition, eventually to maximize quality of life [19], and have been identified as useful for individuals with chronic conditions such as asthma, heart disease, diabetes [19,20]. However, due to several reasons, results of studies relating to chronic patient groups cannot be generalized to patients with epilepsy. For example, the consequences of poor self-management, i.e. not taking AEDs or irregular sleeping patterns, are not always directly observable; seizure deregulation can appear the same day or a couple of days later. Hence, the direct link between poor disease management and the frequency of seizures is not transparent for epilepsy patients. A recent study showed that many patients with epilepsy seem to be unaware of missed doses, indicating the need for pill dispensers and reminding/educational interventions [21].

Self-efficacy, defined as the confidence to carry out a behavior necessary to reach a desired goal [19] an important concept in self-management. Self-efficacy and changes in self-efficacy are associated with future health status and it appears that enhanced self-efficacy is at least one of the mechanisms responsible for the improvements in health status demonstrated by those attending self-management programs [22-24]. Working within the field of epilepsy, Pramuka et al. [20]. piloted a psychosocial self-management program for epilepsy and observed a positive correlation between self-efficacy and quality of life. In addition, Amir et al. [18] emphasized the possibility of increasing quality of life among patients with epilepsy by counseling and treatment aimed at increasing their self-efficacy. However, the Managing Epilepsy Well network recently concluded that too few self-management programs exist in general and that there are too few evidence-based programs available [25].

This study will therefore evaluate the feasibility and (cost-)effectiveness of a multi-component intervention (MCI), which combines a self-management/education program with e-Health interventions, aiming to improve self-efficacy and concordance in people with epilepsy, in comparison with care as usual (CAU). Hence the MCI focuses on increasing patients’ understanding of their medical regimens, and on providing skills and tools to strengthen self-management and communication between patient and healthcare professional and increase adherence (as a proxy for concordance).

## Methods

This study will consist of three parts, each with its own research questions:I.Clinical effectivenessIs MCI, in comparison with CAU, more effective in terms of self-efficacy and other patient-reported outcomes (self-efficacy, adherence, decrease in seizure frequency & severity, side effects of AED, controlling depression/anxiety, proactive coping, improved quality of life, and societal costs)?Does the MCI have a clinical superiority over CAU in terms of a better adherence to AEDs?II.Economic evaluation3)What is the cost-effectiveness and the cost-utility of the MCI in comparison with CAU from a societal perspective?III.Process evaluation4)Has the MCI been delivered according to protocol? And if not, what are the reasons for protocol deviation?5)What are the experiences and opinions of patients, caregivers and professionals regarding the MCI?6)To what extent has the MCI impacted concordance among patients (i.e. do patients understand why it is relevant to take the AEDs, and has the MCI impacted shared decision making by means of consensual agreement between patient and doctor regarding the medical regimen?)

## Design

A randomized controlled trial (RCT) with two parallel groups will be conducted to compare the MCI with a control situation in epilepsy patients. Patients assigned to the intervention group will attend the MCI consisting of five weekly sessions and one booster session. The control group will receive CAU as naturally as possible. The follow-up of patients in the intervention group will be 12 months and the follow-up of patients assigned to the control group will be 6 months, after which patients in the control group have the opportunity to receive the MCI outside the study (see Figure 1). The study has been approved by the Ethics Committee of University Hospital Maastricht, the Netherlands.

**Figure 1 Fig1:**
[figure not shown]
**Schematic representation of study design.**

### Study population

One hundred eligible epilepsy patients will be included in the study. Eligible patients are adults aged 18 or over, living at home, diagnosed with epilepsy and using AEDs, who understand the Dutch language, and are willing and able to use e-Health devices belonging to the MCI. Patients will be excluded if they are not able or willing to function in group activities or when it is expected, on the basis of clinical judgment, that patients are not able to comprehend topics discussed within the MCI (i.e. patients with cognitive deficits).

### Setting and recruitment

This study is a collaboration between Maastricht University and the epilepsy center Kempenhaeghe (KH). The study will be conducted at the outpatient clinics of KH. The first MCI will be offered at the outpatient clinic at the main location of KH (Heeze), after which the MCI will be offered at other outpatient clinics (i.e. Nijmegen and Maastricht). From April 2014 onwards, neurologists and nurse practitioners (NP) will recruit possible candidates for participation during consultations at the outpatient clinics of KH. Furthermore, a press release will be published in national epilepsy magazines and on social media, and patient information leaflets will be distributed to patients in the outpatient clinics of KH. In the press release patients are invited to send their contact information to the researchers.

When patients show interest in participating, an information meeting will be scheduled with one of the researchers ([name] or [name]), either by phone or face-to-face, in which patients will have the opportunity to ask questions and in which inclusion and exclusion criteria will be checked either by the researchers during the meeting or afterwards in consultation with clinicians. During the meeting, patients are informed about the study and that they will be randomly assigned either to the intervention or control group. After one week researchers will contact patients who have received information and want to take part in the study to plan a visit. During this visit an informed consent form will be signed by the patient and the researcher, and patients will be allocated randomly to either the intervention or control group.

### Sample size

The primary outcome variable of this study will be self-efficacy as measured on the Epilepsy Self-Efficacy Scale 33 (ESES) [26]. In a previous pilot study exploring the effects of a psychosocial self-management program for epilepsy patients, with self-efficacy as the primary outcome, the difference between groups was approximately 10 points, with a standard deviation of 7 points on the ESES [20]. Assuming that alpha = 0.05 and power p = 0.90, a minimally detectable difference of 5 points between the intervention and control groups, we will need to include 42 patients per group. Based on a dropout rate of 20% we intend to include 50 patients in each group.

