### Randomization

Patients will be randomized to the MCI (intervention group) or to the control group, in which patients will be given the opportunity to attend the MCI outside of the study after six months of follow-up. For parallel provision of both groups (intervention & control), two blocks of five patients are needed at the moment of randomization. Patients will be assigned to the intervention group or the control group by means of block randomization, using blocks of 10 patients. An assistant who is not involved in the treatment nor in the trial will execute the procedure with a randomization program (www.randomization.com).

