## Analysis

### Clinical effectiveness

Baseline characteristics will be described, and differences between groups at baseline will be studied using t-tests or chi-square tests where appropriate. All statistical procedures will be conducted based on both the intention-to-treat principle and on actual participation in treatment (i.e. effectiveness analyses) and will be performed using SPSS statistics 22.0 (SPSS, IBM, Corporation, Chicago, USA). Missing data will be handled using SPSS missing value analysis on item level. Completely missing measurements will be handled using multiple imputation. To evaluate outcomes, change scores will be calculated and compared between the groups after treatment. Multi-level analyses will be performed with measurements (T0, T1, T2, T3 and T4) within the subjects’ factor and group and between subjects’ factors to account for the nested structure of the data. Data from the control group will be extrapolated to 12 months. Post hoc analyses will be performed in case of significant effects. Baseline differences will be corrected by inclusion of covariates in the analyses. A 2-sided significance level of 0.05 will be used as a threshold to determine whether differences are statistically significant.

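### The 20% dropout allowance is miscalculated: 50 per group leaves 40, not the required 42, though the effect on power is small

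*Protocol article*

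**What the plan says.** The Sample size section of the protocol article gives the full chain for the primary outcome, the Epilepsy Self-Efficacy Scale (ESES).

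- Error rate and power: "Assuming that alpha = 0.05 and power p = 0.90". The Clinical effectiveness part of the Analysis section makes the test two-sided: "A 2-sided significance level of 0.05 will be used as a threshold".
- Target effect: "a minimally detectable difference of 5 points between the intervention and control groups".
- Variability, taken from a pilot study: "with a standard deviation of 7 points on the ESES".
- Number required: "we will need to include 42 patients per group".
- Allowance for loss: "Based on a dropout rate of 20% we intend to include 50 patients in each group".

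The total is repeated under Study population ("One hundred eligible epilepsy patients will be included in the study") and in the Abstract, so 50 per group is not a misprint.

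**The concern.** A dropout allowance should ensure that the required number remains after the assumed loss. Here the requirement (42), the assumed loss (20%) and the enrolment (50) stand in consecutive sentences and cannot all hold. The base calculation leaves no room for rounding, because 42 is the smallest whole number per group that reaches 90% power by the method used.

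At stake is the accuracy of the trial's own sample size statement: as printed, it implies that 90% power survives 20% dropout.

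**Working it through.** **Inputs** (Sample size section; sidedness from Analysis, Clinical effectiveness): difference 5 points, SD 7 points, two-sided alpha 0.05, power 0.90, dropout 20%, 50 enrolled per group. Allocation is equal, since the Randomization section says "two blocks of five patients are needed at the moment of randomization".

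**Step 1: reproduce the plan's 42.** With the normal approximation,

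n = 2 × (SD/difference)² × (z₀.₉₇₅ + z₀.₉₀)² = 2 × (7/5)² × (1.960 + 1.282)² = 41.2, so 42 per group.

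This agrees with the plan. A one-sided test would give 34 and 80% power would give 31, so two-sided 90% is clearly the intended basis. An exact t-test calculation gives 42.2. The fault is therefore in the dropout step and not before it.

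**Step 2: the dropout step.**

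- What 50 leaves: 50 × (1 − 0.20) = 40 per group.
- What 42 needs: 42/(1 − 0.20) = 52.5, so 53 per group, 106 in total.
- What gives 50: 42 × 1.20 = 50.4.
- Dropout at which 50 still leaves 42: 1 − 42/50 = 16%.

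**Step 3: effect on power and detectable difference.** For the normal approximation at 40 per group, the standard error is 7 × √(2/40) = 1.565, and 5/1.565 = 3.194. Power is Φ(3.194 − 1.960) = 89.1%. The difference detectable with 90% power is 1.565 × (1.960 + 1.282) = 5.07. The t-test figures use the noncentral t distribution.

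| Patients per group | Power, normal approx. | Power, t-test | Detectable difference at 90% power, normal approx. | Same, t-test |
|---|---|---|---|---|
| 42 (stated need) | 90.5% | 89.9% | 4.95 | 5.01 |
| 41 | 89.9% | 89.2% | 5.01 | 5.07 |
| 40 (50 less 20%) | 89.1% | 88.4% | 5.07 | 5.14 |

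Like for like, going from 42 to 40 costs about 1.4 percentage points (normal approximation) or 1.5 (t-test). The two methods should not be mixed. The normal approximation pairs 53 per group with 89.1%. The t-test needs 43 completers (42.2 rounded up), hence 43/0.80 = 53.75, so 54 enrolled, and pairs that with 88.4%.

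**The case against.** The strongest objection is that this hardly matters. By the plan's own method, power at 40 per group is less than one point below 90%, and the shortfall arises only if dropout really exceeds 16%. The 5-point target is already half the pilot difference of about 10 points, so a shift to 5.07 or 5.14 points is immaterial. The intervention runs in groups of five with randomization blocks of ten, so 50 per group is a natural operational number. All of this stands, and it makes the point minor.

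A second objection is that dropouts are not simply discarded. The Analysis section plans intention-to-treat analysis, multiple imputation, multi-level modelling of repeated measurements and baseline covariates, so a patient lost after the 3-month visit still contributes. This is fair as a caution against treating the effective sample as exactly 40. It does not repair the arithmetic, because the sample size statement itself treats dropouts as lost and the article gives no figure from which a gain could be calculated.

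A reader might go further and infer that the trial lacks its stated power or is underpowered. The document does not support that. The loss is conditional on an assumed dropout rate, amounts to about 1.5 points, and disappears at 16% dropout or less.

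**Conclusion.** The dropout allowance is wrong as written. At 20% dropout, 50 per group yields 40 and not 42, and keeping 42 would require 53. No other part of the article corrects this. The size is small: power of 89.1% (normal approximation) or 88.4% (t-test), and a detectable difference of 5.07 or 5.14 points in place of 5.

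These figures rest on the plan's own inputs (difference 5, SD 7, two-sided 0.05), on a simple comparison of two means, and on dropouts contributing no information. That 50 came from multiplying by 1.20 is an inference from the match with 50.4, since the article does not show its formula. This is a minor correction to a planning statement and does not call the design into question.

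**What to change.** Keep 100 patients and replace the last sentence of the Sample size section with wording such as: *Fifty patients per group retains the required 42 per group with up to 16% dropout; with 20% dropout (40 per group), power for a 5-point difference is about 88–89%.* Name the method: 89.1% for the normal approximation, 88.4% for the t-test.

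The cost is one sentence and a slightly less favourable stated power. Recruitment, randomization and analysis are unaffected.

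Only if 90% power at 20% dropout must be guaranteed as stated does the number rise, to 53 per group by the method that gives 42. In complete blocks of ten the total of 106 becomes 110. A gain of about 1.5 points of power would not by itself justify that.

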### Randomization

Patients will be randomized to the MCI (intervention group) or to the control group, in which patients will be given the opportunity to attend the MCI outside of the study after six months of follow-up. For parallel provision of both groups (intervention & control), two blocks of five patients are needed at the moment of randomization. Patients will be assigned to the intervention group or the control group by means of block randomization, using blocks of 10 patients. An assistant who is not involved in the treatment nor in the trial will execute the procedure with a randomization program (www.randomization.com).

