### Group sessions

The MCI is offered as a group treatment to groups of 5 patients and additional family members and/or friends. The MCI will last 9 weeks. During the first 5 weeks, group sessions will take place once a week, followed by a booster session 3 weeks later. The group sessions last 2-2.5 hours and are led by an NP with experience in working with epilepsy patient groups. The first session is aimed at providing information about the MCI, including materials, and getting to know the other participants and therapists. During the next sessions, participants will practice with the five stages of proactive coping defined by Aspinwall & Taylor [31]. These five stages are (1) resource accumulation, (2) recognition of potential stressors, (3) initial appraisal, (4) preliminary coping efforts, and (5) elicitation and use of feedback concerning initial efforts.

The model will be applied by the patients to three fixed epilepsy-related themes. The first theme will be self-monitoring and self-monitoring (e-Health) tools. The other two themes will be risk-management and shared decision-making/concordance.

Each group session will have the same basic structure. The sessions will begin by looking back at goals set in the previous meeting and how things have worked in the last week. Next, the theme of the session will be introduced. Patients and caregivers will be invited to share their beliefs, emotions and experiences with regard to the theme. Subsequently, patients and caregivers will formulate their own action plan in order to attain a goal relevant to the theme. Patients will be instructed to keep their goals feasible, and group members will give feedback on the quality of the goals in terms of concreteness and attainability. They will help each other to recognize additional conditions and barriers which need to be addressed. After the feedback discussion, patients and caregivers will formulate their final plan.

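### Patients are randomised in batches of ten, but the stated model has no block term; alone this makes the standard error slightly too wide, and the net direction is open because therapy groups are also unmodelled

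*Protocol article*

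**What the plan says.** - **Randomization.** Allocation is in tens: "Patients will be assigned to the intervention group or the control group by means of block randomization, using blocks of 10 patients". The reason given is practical. The two conditions run in parallel, so "two blocks of five patients are needed at the moment of randomization".
- **Setting and recruitment.** The programme starts at the main location, "after which the MCI will be offered at other outpatient clinics (i.e. Nijmegen and Maastricht". Neither section mentions stratification by clinic or says that a block is drawn from one clinic.
- **Group sessions.** "The MCI is offered as a group treatment to groups of 5 patients and additional family members and/or friends". Control patients have no comparable grouping.
- **Analysis, Clinical effectiveness.** "Multi-level analyses will be performed with measurements (T0, T1, T2, T3 and T4") within subjects and group between subjects. The stated aim is "to account for the nested structure of the data", but the only nesting named is measurements within patients. Covariates enter by one rule: "Baseline differences will be corrected by inclusion of covariates in the analyses". For testing, "A 2-sided significance level of 0.05 will be used as a threshold".

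**The concern.** A block of ten is a batch of patients who enter at the same time, five per arm. If it also comes from one clinic, both arms of the block share calendar period, clinic and local usual care. Such shared variation cancels in the comparison of arms, because every block contributes equally to each. A model without a block term leaves it in the residual, so the standard error is larger than the design warrants.

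The covariate rule does not repair this. It looks for differences between arms at baseline. Block membership is identical in the two arms by construction, so no baseline comparison can flag it.

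At stake is a little precision in a trial of 50 per arm, and agreement between the analysis and the randomisation. The same batches also carry the therapy groups, so the block question cannot be settled without them.

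**Working it through.** **Inputs from the article.** Blocks of 10; therapy groups of 5; 50 patients per arm; two-sided 0.05; power 0.90; difference 5 and SD 7 on the epilepsy self-efficacy scale. **Assumed:** the variance shares of block (b) and therapy group (g), each tried from 0 to 0.10, because the article gives neither.

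**1. The plan's own figure.** n per arm = 2 × (7/5)² × (1.960 + 1.2816)² = 2 × 1.96 × 10.507 = 41.19, rounded up to 42. This reproduces the stated 42, which treats patients as independent.

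**2. Structure.** 100/10 = 10 blocks and 50/5 = 10 therapy groups, so one therapy group per block.

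**3. Formulas.** Set total variance to 1 and e = 1 − b − g, with K = 10 blocks, m = 5 and n = 50. This treats one between-arm comparison with complete data.
- True variance of the difference: 2e/n + g/K. The block effect cancels.
- Expected variance estimate with neither term: (2e + 2bf + gf)/n, where f = (1 − m/n) × n/(n − 1) = 0.9 × 50/49 = 0.918.

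**4. Block effect alone (g = 0).**

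| b | Estimated variance | True variance | SE ratio |
|---|---|---|---|
| 0.02 | (1.96 + 0.0367)/50 = 0.03993 | 0.0392 | 1.009 |
| 0.05 | (1.90 + 0.0918)/50 = 0.03984 | 0.0380 | 1.024 |
| 0.10 | (1.80 + 0.1837)/50 = 0.03967 | 0.0360 | 1.050 |

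Simulated type I error is about 4.4–4.6% at b = 0.05 and 4.0–4.2% at b = 0.10. On the sample-size scale, 41.19 × (1 − b) gives 40 per arm at 0.05 and 38 at 0.10, against 42.

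**5. Therapy-group effect alone (b = 0).** The SE ratio is 0.990, 0.951 and 0.907 at g = 0.01, 0.05 and 0.10, so it is too narrow. The variance inflation averaged over the arms is (1 + 4g + 1)/2 = 1 + 2g, and 41.19 × (1 + 2g) gives 43, 46 and 50 per arm.

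**6. Both effects, neither modelled.** At b = g = 0.05, the estimated variance is (1.80 + 0.0918 + 0.0459)/50 = 0.03876 and the true variance is 1.80/50 + 0.05/10 = 0.0410. The ratio is √(0.03876/0.0410) = 0.972, about 3% too narrow. Simulated type I error is 5.6–5.7%. Other combinations (b/g): 0.02/0.05 gives 0.960, 0.05/0.02 gives 1.003, and 0.10/0.05 gives 0.995.

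**7. Break-even.** The two errors cancel when 2bf = g(5 − f), so b/g = 4.082/1.837 = 2.2. The net SE is too wide only if block variance exceeds about 2.2 times therapy-group variance.

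**8. Block term added alone, b = g = 0.05.** The residual mean square averages the within-cell variance e (80 df) and the block-by-arm mean square e + 2.5g (9 df): 0.90 + (9 × 0.125)/89 = 0.9126. The estimated variance is 2 × 0.9126/50 = 0.0365 against 0.0410, a ratio of √0.890 = 0.944. The SE is now about 6% too narrow, and simulated type I error rises to 6.3–6.4%.

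**9. Cost if blocks explain nothing.** Residual degrees of freedom fall from 98 to 89. Power at 50 per arm is 94.2% with or without the block term.

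**10. Dropout.** If the planned 20% fell evenly (four per cell, 40 per arm), f = 0.9 × 40/39 = 0.923. Block alone at 0.05 gives √[(1.90 + 0.0923)/40 ÷ 0.0475] = 1.024, unchanged. Both at 0.05 gives √[(1.80 + 0.0923 + 0.0462)/40 ÷ 0.0500] = 0.984. The pattern stays and the net error shrinks.

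**The case against.** **The omission is small and, alone, errs on the safe side.** This stands. Nobody is led to a false positive by an unmodelled block effect. The article also uses change scores and covariates for baseline, which remove stable differences in level between clinics or waves, so the remaining block share is probably near the low end of the range.

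**A list of model terms belongs in the analysis plan, which is not shown.** This stands in part. Nothing in the article forbids a block term, and the full plan may contain one. But the article does state how covariates are chosen, and that rule cannot select a factor balanced by design. This keeps the point alive, at low severity.

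**One clinic per block is an inference.** This stands. Five patients who must attend weekly sessions together suggest it, but no section says so. If blocks mix clinics, block does not identify clinic.

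**Stronger readings the article does not support.** A reader might infer that the planned analysis as a whole gives standard errors that are too wide. Steps 6 and 7 show that this does not follow, because the unmodelled therapy groups pull the other way and dominate at equal shares. A reader might also cite an inflation of about 7% or 15%. Those figures describe a model with a therapy-group term but no block term, at block shares of 5% and 10%. The article proposes no such model, so they are only a reason to add the two terms together.

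**Conclusion.** The point holds as a minor one. The stated model does not reflect the batches in which patients are randomised, and the covariate rule cannot bring them in. Taken alone, this makes the standard error about 1–5% too wide for an assumed block share of 2–10%, with the low end more likely.

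The net direction under the stated analysis is unknown. It depends on two variance shares that the article does not give. At 5% each the standard error is about 3% too narrow; it is too wide overall only if block variance is more than about 2.2 times therapy-group variance. These results assume ten full blocks of five plus five, one therapy group per block, and a single comparison with complete data.

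**What to change.** 1. **Analysis, Clinical effectiveness:** add randomisation block, fixed or random, to the model for the primary outcome and to the other between-arm models, together with a random effect for therapy group in the intervention arm. Do not add block alone: if therapy groups differ, that raises the type I error (step 8).
2. **Randomization:** state that each block of ten is formed within one clinic, if that is the intention, so that block also identifies clinic and wave.

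**Cost.** Two model terms and one sentence; block and therapy group should be on record for every patient. The block term uses at most 9 degrees of freedom, with almost no loss of power if blocks explain nothing. The therapy-group term will make the interval somewhat wider, since its variance is estimated from only about ten groups. That width reflects uncertainty that the present model leaves out.
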